## Abstract

**Background:**

The bidirectional signaling between the gut microbiota and the brain, known as the gut-brain axis, is being heavily explored in current neuropsychiatric research. Analyses of the human gut microbiota have shown considerable individual variability in bacterial content, which is hypothesized to influence brain function, and potentially mood and anxiety symptoms, through gut-brain axis communication. Preclinical and clinical research examining these effects suggests that fecal microbiota transplant (FMT) may aid in improving the severity of depression and anxiety symptoms by recolonizing the gastrointestinal (GI) tract with healthy bacteria. The microbial ecosystem therapeutic (ie, microbial ecosystem therapeutic-2 [MET-2]) used in this study is an alternative treatment to FMT, which comprises 40 different strains of gut bacteria from a healthy donor.

**Objective:**

The primary objective of this study is to assess subjective changes in mood and anxiety symptoms before, during, and after administration of MET-2. The secondary objectives of this study are to assess the changes in metabolic functioning and the level of repopulation of healthy gut bacteria, the safety and tolerability of MET-2, and the effects of early stress on biomarkers of depression/anxiety and the response to treatment.

**Methods:**

Adults experiencing depressive or anxiety symptoms will be recruited from the Kingston area. These participants will orally consume an encapsulated MET-2 once daily—containing 40 strains of purified and laboratory-grown bacteria from a single healthy donor—for 8 weeks, followed by a 2-week treatment-free follow-up period. Participants will undergo a series of clinical assessments measuring mood, anxiety, and GI symptoms using validated clinical scales and questionnaires. Molecular data will be collected from blood and fecal samples to assess metabolic changes, neurotransmitter levels, inflammatory markers, and the level of engraftment of the fecal samples that may predict outcomes in depression or anxiety.

**Results:**

Given the association between the gut bacteria and the risk factors of depression, we expect to observe an improvement in the severity of depressive and anxiety symptoms following treatment, and we expect that this improvement is mediated by the recolonization of the GI tract with healthy bacteria. The recruitment for this study has been completed, and the data obtained are currently being analyzed.

**Conclusions:**

This is the first time MET-2 is being tested in psychiatric indications, specifically depression and anxiety. As such, this may be the first study to show the potential effects of microbial therapy in alleviating psychiatric symptoms as well as its safety and tolerability.

**International Registered Report Identifier (IRRID):**

DERR1-10.2196/17223

## Introduction

### Depression and Anxiety

Major depressive disorder (MDD) is the leading cause of disability worldwide and is a major contributor to the overall global burden of diseases [1]. Globally, over 300 million people of all ages are affected by MDD over their lifetime, and the mortality risk of suicide for these individuals is 20-fold greater than that of the general population [2]. MDD is characterized by either a persistent depressed mood or loss of interest or pleasure in surroundings accompanied by a variety of symptoms that cause clinically significant distress or impairments [3]. MDD may have a severe and chronic course, with the majority of affected individuals subjected to multiple recurrent episodes throughout their lifetime as well as academic, occupational, and interpersonal functioning impairments and high levels of medical and psychiatric comorbidities [4].

A common comorbidity in individuals with MDD is generalized anxiety disorder (GAD). GAD is characterized by excessive anxiety and worry, particularly due to life circumstances, such as work, school, and relationships [5]. GAD is one of the most common and the broadest anxiety disorder affecting 3% of the general population in 1 year, with a lifetime prevalence of 5% [6,7]. The psychological symptoms of GAD can also be accompanied by physical symptoms, such as abdominal pain, muscle tension, restlessness, or sleeping problems. The association between generalized anxiety and gastrointestinal (GI) symptoms may be explained by the close connection between the gut and the brain.

### Gut Brain Axis

In the last several years, there has been a growing appreciation for research in the field of the *gut****-****brain axis*, which consists of bidirectional signaling between the GI tract and the brain. Over 100 trillion commensal bacteria are estimated to exist symbiotically in the human gut and are critical in the normal development of the immune system, central nervous system (CNS) circuitry, GI functioning, and autonomic nervous system functioning [8]. Detailed analyses of human gut microbiota have shown considerable individual variability in bacterial content, as this dynamic system is influenced by a variety of factors, such as genetics, diet, metabolism, age, geography, antibiotic treatment, and stress [8]. Studies have also shown that human gut bacteria play a vital role in regulating important aspects of brain development and function, along with other host physiology [9,10].

By being able to shape brain physiology and, therefore, behavior through gut**-**brain axis communication, gut bacteria may be a vital trigger in the development of neuropsychiatric conditions [11]. Given the adaptable nature of the gut microbiome, it may be a good representation of the individual’s history and could explain the differences in risk of illness, disease course, and response to treatment. The interaction of the gut with the environmental risk factors of depression and anxiety, such as diet and early life stress, also suggests that interventions that target the gut microbiome could prevent and treat depression and anxiety symptoms [12]. In past studies, depressed patients have been shown to have a dissimilar microbiota composition compared with healthy individuals due to the decreased diversity and abundance of their gut microbiota [13-15].

### Gut Microbiome and Psychiatric Symptoms

MDD pathophysiology involves three different physiological systems: (1) neurotransmitter dysfunction between the prefrontal cortex regions in the CNS and the hypothalamic-pituitary-adrenal (HPA) axis, (2) chronic inflammation of the immune system, and (3) an imbalance in the microbiota-gut**-**brain axis [16-20]. The prefrontal cortex, hippocampus, and amygdala play a vital role in the regulation of emotion, anxiety, stress responses, self-control, motivation, and cognitive reactions. However, in depressed patients, the function of the prefrontal cortex and hippocampus is impaired, whereas the activity of the amygdala is increased [21]. These arguments are supported by the monoaminergic neurotransmitter deficiency hypothesis, which postulates that monoamine neurotransmitters serotonin (5-HT), norepinephrine (NE), and dopamine (DA) are at insufficient levels and ultimately result in depressive symptoms. The immune system plays an important role in depression; the cytokine and neuroinflammation hypotheses suggest an increase in pro-inflammatory cytokines (interleukin 6 [IL-6] and tumor necrosis factor alpha [TNF-α]), and a decrease in anti-inflammatory cytokines (interleukin 10 [IL-10] and transforming growth factor beta [TGF-β]), contribute to a pro-inflammatory state in depressed patients. These cytokines inhibit the negative feedback of the HPA axis, increase the permeability of the blood-brain barrier, reduce the synthesis of 5-HT, disturb the glutamatergic systems, and influence neuroglial cells. These actions play a vital role in the regulation of neuro-immunity and neuroplasticity and are hypothesized to result in depressive behavior [22-27]. In 2012, Maes et al [28] showed that bacterial translocation from the gut, or *leaky gut*, which may be due to systemic inflammation in depression or may be a primary trigger that is associated with the onset of depression, can activate immune cells to elicit selective immunoglobulin A (IgA) and immunoglobulin M (IgM) response—both antibodies that fight and protect against infections. The results of this study suggest that this phenomenon may be involved in the pathophysiology of depression by causing progressive amplifications of immune pathways [28].

### Microbial Ecosystem Therapeutics

Despite increasing research, a complete understanding of gut microbial changes is still lacking. Interestingly, depressive symptoms have been shown to be transmissible via fecal microbiota transplantation (FMT) in animal models [29]. Zheng et al [30] demonstrated that FMT material from depressed but not neurotypical human patients resulted in depressive-like symptoms upon transfer to germ-free recipient mice. Given that disturbances to the gut microbiome can increase susceptibility to depression, repopulating the gut microbiome may allow for improvement in mood and anxiety symptoms. Microbial ecosystem therapeutic-2 (MET-2) is a new treatment approach for repopulating the gut with healthy bacteria that has been developed as an alternative to FMT. This is a biological compound comprising live microbes that normally reside in the gut of a healthy individual. Given that stool contains a highly complex and dense community of microbes, including bacteria, fungi, and viruses, many of which have not been fully characterized, the product focus of MET-2 is on defined mixtures of isolated strains of intestinal bacteria as the treatment [31]. MET-2 capsules contain 40 strains of purified lyophilized bacteria from a healthy 25-year-old donor, chosen for their favorable safety profile. MET-2 capsules are produced under conditions compatible with good manufacturing practice, at the University of Guelph, sealed under anaerobic conditions, and shipped at room temperature. The vials of MET-2 capsules are transferred at room temperature from the University of Guelph to the Providence Care Hospital pharmacy. The investigator ensures that the product is stored at room temperature ready for use in appropriate conditions and in a secure, locked storage with controlled access until use. Capsules are used to improve MET-2’s appeal to participants to allow for easier administration over consecutive days, in contrast to FMT, which involved of rectal administration. Moreover, capsules allow for oral administration of controlled fecal colonies, which confers an increased level of safety over the use of raw fecal material administered via rectal suspension. This protocol will outline a phase 1, open-label clinical trial that will assess the safety, efficacy, and tolerability of MET-2 on depression and anxiety symptoms.

### Objectives

#### Primary Objective

The primary objective of this study is to assess subjective changes in mood and anxiety symptoms before, during, and after MET-2 treatment in participants with major depression and/or generalized anxiety, using the Montgomery-Asberg depression rating scale (MADRS), GAD 7-item scale (GAD-7), and other mood/anxiety scales. Those with a 50% reduction in the GAD-7 and/or MADRS scores will be considered successful responders to treatment.

#### Secondary Objectives

The secondary objectives are to assess changes in metabolic functioning/levels before, during, and after treatment; to assess safety and tolerability, including adverse events (AEs) with a severity of grade 2 or above; and to assess potential correlation between early life stress (childhood emotional/physical/sexual abuse history, etc) and changes in MDD biomarkers as well as response to treatment.

## Methods

### Study Design

This is an 8-week, open-label, phase 1 clinical trial assessing the safety, tolerability, and efficacy of MET-2 on depression and anxiety symptoms. All participants will consume the investigational product, MET-2, in *a* capsule form, daily for 8 weeks. MET-2 is administered orally at 0.5 g of MET-2 per capsule, containing 3.2 ×10^5^-3.2×10^11^ colony-forming units (CFUs). At each in-hospital visit, participants take home the appropriate number of MET-2 capsules needed for a 2-week period, packaged in bottles. Loading/booster doses are provided in separate vials from maintenance daily doses. Each vial is stored by the participant at room temperature. MET-2 is meant to be taken after a light meal, preferably in the morning and at the same time every day.

Participants will consume an initial loading dose of 5 g MET-2. An initial MET-2 dose in the range of 10^8^ to 10^12^ CFUs was selected with the aim of ensuring delivery of a sufficient quantity of the MET-2 bacterial community that is expected to colonize the gut. The first loading dose, at baseline, is to be consumed under the supervision of the study staff to ensure immediate safety, and further compliance is assessed using the returned investigational product and by reviewing participants’ personal logs at each in-hospital visit. For the remainder of the 2-week period, the participants will consume 1.5 g of MET-2 per day. The loading dose is repeated for the first 2 days at the week 2 time point, and participants return to the maintenance dose for the remainder of the treatment period. At week 4, participants are assessed for treatment response. Responders remain on the maintenance dose until the end of treatment. Nonresponders are given an additional loading dose (booster dose; Table 1).

**Table 1 table1:** Dosing schedule.

Dose	Baseline to week 2	Weeks 2*-*4	Weeks 4*-*6	Weeks 6*-*8
Loading/booster dose (5 g of MET-2^a^: 10 capsules per day for 2 days)	Days 1 and 2 only	Days 1 and 2 only	Days 1 and 2 (only NR^b^)	N/A^c^
Maintenance dose (1.5 g of MET-2: 3 capsules per day)	Days 3-14	Days 3-14	R^d^: Days 1-14; NR: Days 3-14	Days 1-14

^a^MET-2: microbial ecosystem therapeutic-2.

^b^NR: nonresponders.

^c^N/A: not applicable.

^d^R: responders.

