#### Treatment Success

Treatment success is defined as a reduction in the MADRS/GAD-7 scores by 50% from the baseline. Those who do not meet the 50% threshold are considered nonresponders. Nonresponders at the week 4 visit will be given a booster dose.

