### Statistical Analyses

Treatment success and failure will be measured individually. Those who have an improvement of at least 50% in MADRS or GAD-7 scores will be considered responders. The SPSS will be used to analyze all data from clinical measures obtained throughout the study. Repeated measures analysis of variance (ANOVA) will be used to analyze changes in clinical measures from baseline to week 10. Paired *t* tests will be used to compare clinical measure means at each time point with the baseline. If a participant returns after the first course of treatment and is later withdrawn, their final scores for primary outcomes will be projected to week 10. In the event of missing data, the data from the last time point will be projected forward. Similarly, stool samples will be analyzed to provide diversity scores, which will then be compared using paired *t* tests and repeated measures ANOVA. Changes in diversity scores will be compared with clinical scores to assess for correlations.

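### The week-4 booster is assigned by the primary outcome, so week-8 and week-10 correlations of diversity change with symptom scores can be confounded by the dosing rule

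*Protocol article*

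**What the plan says.** The dosing rule is in the protocol article under Study Design, Table 1 and the Treatment Success definition. All participants have the same schedule for the first four weeks, including two loading courses. At week 4 the schedule divides: "Responders remain on the maintenance dose until the end of treatment", whereas "Nonresponders are given an additional loading dose (booster dose; Table 1"). The Treatment Success definition repeats the rule: "Nonresponders at the week 4 visit will be given a booster dose". The dividing line is a primary-outcome criterion: "Treatment success is defined as a reduction in the MADRS/GAD-7 scores by 50% from the baseline".

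The microbiome analysis is in Statistical Analyses. Stool diversity scores are to be analysed with paired t tests and repeated measures ANOVA, and then "Changes in diversity scores will be compared with clinical scores to assess for correlations". No visits are named for the correlation and the booster is not mentioned. The same section analyses clinical measures from baseline to week 10 and classifies responders individually.

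The abstract gives the mechanistic expectation: "we expect that this improvement is mediated by the recolonization of the GI tract with healthy bacteria". The Results section of the article likewise expects mediated improvement from baseline to week 10, and a donor-like microbiome by the end of the study.

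Table 2 schedules stool samples at weeks 0, 2, 4, 8 and 10, and MADRS and GAD-7 at every visit.

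**The concern.** The booster repeats the loading dose, and Study Design says the initial loading dose was sized to deliver enough bacteria to colonise the gut. After week 4 that extra exposure goes to all participants who have improved least and to none of those who have improved most. If it moves the stool measure, the weaker improvers will show the larger late microbiome change because of the rule, whatever the true relation between microbiome and mood.

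At stake is the mechanistic conclusion. Two of the four post-baseline stool samples (weeks 8 and 10) follow the booster, and these bear most directly on the stated end-of-study expectation. A late correlation near zero could mean no association, or a real one offset by outcome-driven dosing. Adjusting for booster receipt cannot settle which, because receipt coincides exactly with week-4 nonresponse.

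**Working it through.** **1. Dose by week-4 status.** Inputs from Study Design and Table 1: 0.5 g per capsule; loading or booster 10 capsules a day for 2 days; maintenance 3 capsules a day.

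- Daily doses: 10 x 0.5 = 5 g and 3 x 0.5 = 1.5 g, which agree with the article.
- Fortnight with loading: 2 x 5 + 12 x 1.5 = 28 g. Maintenance fortnight: 14 x 1.5 = 21 g.

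| Period | Week-4 responders | Week-4 nonresponders | Difference |
|---|---|---|---|
| Weeks 0-4 | 28 + 28 = 56 g | 28 + 28 = 56 g | 0 |
| Weeks 4-6 | 21 g | 28 g | +7 g (33%) |
| Weeks 4-8 | 21 + 21 = 42 g | 28 + 21 = 49 g | +7 g (17%) |
| Weeks 0-8 | 98 g | 105 g | +7 g (7%) |

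Exposure is identical to week 4 and depends on the outcome afterwards.

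**2. Time from booster to the next stool sample.** Table 2 has no week-6 stool sample, although Molecular Analysis says stool is collected at all in-hospital visits; the two need reconciling. On Table 2, the first post-booster sample is at week 8, after 12 + 14 = 26 days of maintenance dosing common to both groups.

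**3. Size of the induced correlation.** The article gives no booster effect on diversity, so this is an illustration. Assumptions, none from the article:

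- week-4 and week-8 improvement are standard normal with correlation ρ = 0.5 to 0.8;
- a proportion p = 20% to 50% respond at week 4;
- diversity change at week 8 is standard normal noise plus a shift of b SD in booster recipients;
- there is no true link between diversity and symptoms.

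Let c be the normal cut-off exceeded with probability p, and φ(c) the density there. The covariance of diversity change with week-8 improvement is -bρφ(c), and the variance of diversity change is 1 + b²p(1-p). Hence

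r = -bρφ(c) / √(1 + b²p(1-p)).

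- b = 0: r = 0.
- b = 0.5, p = 0.2, ρ = 0.5: φ(c) = 0.280, so r = -0.070 / √1.04 = -0.07.
- b = 0.5, p = 0.5, ρ = 0.8: φ(c) = 0.399, so r = -0.160 / √1.0625 = -0.15.
- b = 1, same two settings: r = -0.140 / √1.16 = -0.13, and r = -0.319 / √1.25 = -0.29.

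Negative here means that more diversity goes with less improvement. If raw scores are correlated instead, where lower is better, the sign reverses.

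**4. Effect on a true correlation of 0.50.** With the shift added,

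r = (0.5 - bρφ(c)) / √(1 + b²p(1-p) - bρφ(c)).

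- b = 0.5: from 0.430 / √0.970 = 0.44 down to 0.340 / √0.903 = 0.36.
- b = 1: from 0.360 / √1.020 = 0.36 down to 0.181 / √0.931 = 0.19.

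**5. Scale against sampling error.** The planned sample is 10 to 15, and the article reports 12 participants completing with at least one post-baseline visit. The two-sided 5% critical |r| is 0.63 at n = 10, 0.58 at n = 12 and 0.51 at n = 15. Simulation at n = 12 with p = 35% and ρ = 0.7 gives a type I error of about 6.8% at b = 0.5 and 10.6% at b = 1, against a nominal 5%.

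**The case against.** Much of the case against a stronger claim stands.

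- **No responder comparison is planned.** A reader might infer that responders and nonresponders are to be compared after week 4. Statistical Analyses only classifies individuals, and the secondary objectives relate early life stress to biomarkers and response. No between-group test is written.
- **The main clinical analyses are not confounded.** A reader might also infer that pooling everyone in the ANOVA and paired t tests is a flaw. These are within-participant estimates for the whole cohort under the regimen as designed, booster included. That late improvement cannot be divided among booster, maintenance and time reflects the lack of a control arm, and the Discussion already lists the missing placebo arm as a limitation.
- **Size and direction are not established.** The extra dose is 7% of the course, follows two loading courses given to everyone, and must leave a shift lasting at least 26 days. The planned variable is diversity, not abundance of the product strains; more of a 40-strain product need not raise diversity. If it lowered diversity, the bias would change sign. Even at 0.5 SD it is small beside sampling error.

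It can also be said that the choice of visits belongs in an analysis plan not shown here, and that a baseline-to-week-4 correlation already fits the sentence. That is true of detail as such. But the article itself fixes both the outcome-driven dosing and an undivided correlation, and rests its mechanistic expectation on end-of-study data. The conflict lies in that combination, and a small sample does not remove the bias.

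**Conclusion.** The point holds in a limited form. Exposure after week 4 is a deterministic function of the week-4 primary outcome, so correlations of week-8 or week-10 diversity change with clinical scores can be confounded by the dosing rule. If the booster raises diversity, a favourable association is pulled toward zero. The size may be nil. On the stated assumptions it is about -0.07 to -0.15 for a 0.5 SD shift and -0.13 to -0.29 for a 1 SD shift, in each case only if the shift persists to week 8.

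Correlations up to week 4 are unaffected. Week-8 and week-10 change and response remain valid as descriptions of the response-adapted regimen, but should not be credited to a fixed schedule.

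**What to change.** In Statistical Analyses:

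1. Specify a baseline-to-week-4 correlation of diversity change with MADRS and GAD-7 change as the analysis free of outcome-driven dosing. Stool and both scales are already scheduled at week 4. Confirm that each week-4 stool sample was produced before the first booster capsules.
2. Report week-8 and week-10 correlations alongside it as descriptive, with booster recipients identified (for example by plotting symbol). Do not compute separate correlations by booster status: that would stratify on the outcome, in very small groups.
3. Describe week-8 and week-10 change and response as obtained under the response-adapted regimen.
4. Recruitment is complete and analysis is under way, so date and disclose this as a late change.

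The response criterion is joined by and/or in the Primary Objective, by a slash under Treatment Success and by or in Statistical Analyses. These places must be reconciled so that it is clear who counted as a week-4 nonresponder when only one scale improved.

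The cost is a few sentences and no new data. The downside is that a 4-week window is shorter and may miss later microbiome or symptom change, which is why the later correlations are kept. No change to dosing is implied.
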